## Abstract

Administration of local anesthesia via injection is the main reason for inducing anxiety in children and if not intervened it aggravates the anxiety in subsequent appointments. There are many approaches, including pharmacological and non-pharmacological methods that can be used to reduce children’s perception of pain and anxiety. A frequently used non-pharmacological behaviour management method to reduce anxiety and procedure pain is distraction. The rationale of distraction is to shift the attention to avert the brain from receiving unwanted stimulus which induce anxiousness. Many approaches including music, television, portable video games, virtual reality (VR) helmet, and virtual reality audio-visual eyewear, have been implemented so far. Kaleidoscope and virtual reality goggles may help as distraction techniques in reducing the levels of anxiety caused during administration of local anesthesia. By the aid of which the operator may be able to make the dental experience child friendly and ultimately provide quality dental care to anxious children. Non pharmacological measures of reducing pain are cost effective and best means that can be used while performing dental procedures. This is a research protocol for a study aimed to evaluate and compare the effectiveness of kaleidoscope and virtual reality goggles to reduce dental anxiety in young children.

## Introduction

Anticipation of pain during dental treatment is a frequently reported reason for dental anxiety and fear. Dental anxiety comprises of various physical, mental as well as social components. Anxiety has been defined as a “vague, unpleasant feeling accompanied by a premonition that something undesirable is about to happen”.
^
1
^ In the terms of Dental Fear and Anxiety (DFA), Dental anxiety is characterized as significant negative or unpleasant feeling about a dental office and dental procedures; whereas dental phobia is an irrational form of dental anxiety.
^
2
^ Dental anxiety is said to be a major contributor to poor oral health. Several studies have shown that the majority of significant triggers come from the sight, sound, and vibratory sensation of dental drills, and sensation of a local anaesthetic injection which is a major cause; subsequently dental fear is associated with past painful experiences and negative staff behaviour.
^
3
^ An anxious patient is in a continuous state of restlessness and unease. Children experiencing anxiety during local anesthesia injection gives rise to a significant concern which thus necessitates cognitive - behavioural psychological guidance along with the needed dental treatment.
^
4
^ There are many approaches, including pharmacological and non-pharmacological methods that can be used to reduce children’s perception of pain and anxiety.
^
5
^
^,^
^
6
^ Amongst which the procedures that focuses on cognitive or behavioural methods include practices such as listening to music, dreaming, hypnosis, use of virtual reality goggles, progressive muscle relaxation, and distraction through various interventional techniques.
^
7
^ Attention refers to focusing and processing information from our surroundings. While in anxious state it is important to shift the child’s attention away from the unpleasant stimuli. Distraction works on the principle of diverting the focus and blocking the reception of the unpleasant stimuli that causes anxiety.

Kaleidoscope is an instrument that shows an infinite number of fascinating geometric shapes in the form of a flower, repeating and reflecting images of coloured goggle fragments in the front section in a prism mirroring the inner surface. Increased blinking of the eyes is directly proportional to task difficulty, which in turn produces stress. In a relaxed situation, such as during kaleidoscope viewing, the number of blinks decreases and thus it controls the general physiological excitation.
^
8
^
^,^
^
9
^ Kaleidoscope is being increasingly recognized for its therapeutic and healing value in medical procedures but very few studies on it are available for its use in pediatric dentistry. A study by Aditya
*et al.* was conducted on the pediatric dental population with a kaleidoscope and virtual reality and a positive reduction in VPT scores and pulse rate was reported.
^
10
^

Virtual Reality (VR) is a human–computer interface that enables the user to communicate with the computer-generated atmosphere with dynamism. VR actively involves children and is a potent tool in helping children to keep their attention away from frightening and painful procedures. It allows the children to perceive the environment as a safe where they can be free without any risk.
^
10
^
^,^
^
11
^ Atzori
*et al.* (2017) found that VR technology reduced the mean “worst pain” from 3.80 to 2.20, hence indicating that VR can help effectively distract and engage children undergoing dental treatments.
^
12
^

Hence the focus of this study, according to the available literature, is to evaluate and compare the effectiveness of kaleidoscope and virtual reality goggles to reduce dental anxiety in young children.

### Protocol

The aim of this study is to evaluate and compare the effectiveness of kaleidoscope and virtual reality goggles to reduce dental anxiety in young children undergoing administration of local anesthesia
*.*

Objectives are:
1.To evaluate the effect of kaleidoscope to reduce dental anxiety levels in young children before and after the administration of local anesthesia.2.To evaluate the effect of virtual reality goggles to reduce dental anxiety levels in young children before and after the administration of local anesthesia.3.To compare effect of kaleidoscope and virtual reality goggles technique to reduce dental anxiety levels in young children before and after the administration of local anesthesia.

This parallel randomized multiple-arm clinical trial will be conducted in an isolated setup over a period of six months. It will be a trial for equivalence. Children from five - eight years old who are healthy, co-operative but anxious. Children without any past dental experience those will undergo dental treatment requiring administration of local anesthesia for procedures like pulpectomy or extractions will be included in the study. Children with known vision problems, psychological abnormalities, children with special health care needs, children suffering from systemic diseases, and the parents that are unwilling to participate will be excluded from the study.

**Group 1 – Kaleidoscope:** The children will be given a kaleidoscope having various changing colours and patterns to watch through just before the starting of the procedure and will be asked to watch through it until the procedure ends.

**Group 2 – Virtual reality goggles technique:** The children will be asked to wear Virtual Reality goggles and a video to keep the child engaged will be played by clicking on the remote control. VR will be given just before the starting of the procedure and will be asked to watch through it until the procedure ends.

**Group 3 –** Control group wherein usage of basic behavior guidance techniques like tell-show-do, ask-tell-ask, positive reinforcement, modelling, systemic desensitization and voice control will be employed.

It is a randomized clinical trial. This is a version 1 of the protocol. Sequence generation by lottery method will be generated. The co-investigator of the department will generate the allocation sequence and will assign participants to interventions. It will be a double-blind study where trial participants, data analysts will be blinded. Data management by double data entry will be done. Personal information about potential and enrolled participants will be collected and maintained in order to protect confidentiality before, during, and after the trial. Comparators Kaleidoscope, Virtual reality goggles technique and conventional behaviour management method will be taken into consideration for comparing as all of them are interventions aiding for reducing the anxiety levels.

The sample size calculation is based on previous research by Aditya
*et al.*
^
13
^ that used a similar study technique by using the sample size formula for difference between two means,

$\frac{{\left(z\alpha +z\beta \right)}^{2}\left({\delta_{1}}^{2}+\delta_{2/k}^{2}\right)}{{∆}^{2}}$.

A total of 60 children will be included for the study. The participants in each group will be allocated by simple random sampling.

VFAS score using a validated Visual Facial Anxiety Scale is the primary outcomes to be measured. Pulse oximeter to measure physiological signs of oxygen saturation, and pulse rate, respiratory rate are the secondary outcomes to be measured. All the outcomes will be measured before, during, and immediately after the LA intervention.

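### Objectives 1 and 2 assess each device by before-after change without a comparator, and no objective uses the randomised control arm; answered as written, shared change would be confounded with device effect

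*Protocol article*

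**What the plan says.** The section headed Protocol lists three objectives.

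- Objective 1: "To evaluate the effect of kaleidoscope to reduce dental anxiety levels in young children before and after the administration of local anesthesia".
- Objective 2: "To evaluate the effect of virtual reality goggles to reduce dental anxiety levels in young children before and after the administration of local anesthesia".
- Objective 3: "To compare effect of kaleidoscope and virtual reality goggles technique to reduce dental anxiety levels in young children", at the same two time points.

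The same section defines a third randomised arm: "Control group wherein usage of basic behavior guidance techniques like tell-show-do, ask-tell-ask, positive reinforcement, modelling, systemic desensitization and voice control will be employed". That arm appears in none of the objectives. Further on, the section does mention it: "Comparators Kaleidoscope, Virtual reality goggles technique and conventional behaviour management method will be taken into consideration for comparing". The sentence adds that all three approaches help to lower anxiety. It does not say which pairs of arms are compared, on what measure or by what test.

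Eligibility covers "Children from five - eight years old who are healthy, co-operative but anxious", with no anxiety scale or cut-off given. On timing, "All the outcomes will be measured before, during, and immediately after the LA intervention". The trial is labelled an equivalence trial, with no pair of arms named. The section on data analysis names chi-square and Student's t-tests at p<0.05 and does not say whether the t-test is paired or two-sample.

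**The concern.** A before-after change within one arm contains the device effect plus everything else that changes between the two readings. The article gives several reasons to expect such a component:

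- Children are enrolled because they are anxious, so scores may drift back towards the average.
- The Introduction ties dental anxiety to anticipated pain and calls the injection a major cause. A reading taken once it is over may fall through relief, and a reading taken around it may rise.
- Control children receive active behaviour guidance, so change without either device is foreseeable.

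Only the contrast with control removes this shared component. Objective 3 cannot replace it: two devices with no effect would also look alike. Taken literally, all three objectives could appear to be met although neither device does better than control. If the shared change is a rise, a real benefit could be hidden.

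**Working it through.** **1. The plan's own figure.** The article states 60 children and a two-means formula, n = (z_α + z_β)²(σ₁² + σ₂²/k)/Δ². It gives no power, SD or difference, so 60 can be neither reproduced nor refuted. The allocation ratio is not stated either; 20 per arm (60/3) is assumed below.

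**2. The objectives set against the arms.**

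| Objective | Arms named | Uses control? |
|---|---|---|
| 1 | kaleidoscope | no |
| 2 | VR goggles | no |
| 3 | kaleidoscope, VR goggles | no |
| Comparator sentence | all three | yes, but tied to no objective, contrast or test |

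**3. Why the contrast matters.** Let c be the change common to all arms and d the device effect. The expected within-arm change is c + d. The expected device-minus-control change is (c + d) − c = d. A within-arm result therefore cannot separate c from d.

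**4. Illustration with d = 0, regression to the mean only.** Assumptions, none of them from the article: 20 per arm; baseline and later scores bivariate normal with SD 1 and correlation r; children drawn from the top 50% or top 30% of baseline VFAS; two-sided paired t-test at 0.05.

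- Mean baseline excess: m = φ(cut)/(share selected). For the top 50%, m = 0.399/0.5 = 0.798. For the top 30%, m = 0.348/0.3 = 1.159.
- Variance of the selected baseline: v = 1 + cut·m − m², which is 0.363 and 0.264 respectively.
- Expected fall: (1 − r)m.
- SD of change: √[(1 − r)²v + 1 − r²].
- Standardised fall: f = fall/SD of change. The probability comes from the noncentral t with 19 degrees of freedom and noncentrality f√20.

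| Selected | r | Fall (baseline SD) | f | P(significant fall) |
|---|---|---|---|---|
| top 50% | 0.5 | 0.399 | 0.435 | 0.455 |
| top 50% | 0.7 | 0.239 | 0.325 | 0.281 |
| top 30% | 0.5 | 0.579 | 0.641 | 0.777 |
| top 30% | 0.7 | 0.348 | 0.476 | 0.524 |

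A separate simulation of 20,000 trials gave 0.45, 0.28, 0.78 and 0.52 for the same rows. At r = 0.8 the probabilities are 0.197 (top 50%) and 0.366 (top 30%). With no shared change the figure is 0.025.

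**5. Any shared fall, whatever its cause.** The fall is now expressed in SDs of change, again with d = 0. The last column is 1 − (1 − p)².

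| Shared fall | One arm significant (p) | At least one of two devices |
|---|---|---|
| 0.2 | 0.133 | 0.249 |
| 0.3 | 0.246 | 0.432 |
| 0.5 | 0.564 | 0.810 |
| 0.8 | 0.924 | 0.994 |

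A two-sample t-test of change, device versus control, rejected in 4.9% to 5.1% of 40,000 simulated trials at shared falls of 0, 0.3, 0.5 and 0.8.

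**The case against.** The strongest reply is that the article does foresee a comparison with control. The comparator sentence lists the conventional method, and the sample-size formula is for a difference between two means, which is a between-group quantity. The t-test is not said to be paired, and no within-arm p-value is promised. The before-and-after phrase in objectives 1 and 2 also closes objective 3, which compares arms, so it may only mark measurement times. All of this stands. A reader might infer that the protocol commits to within-arm tests and will ignore the control arm; the text does not support that. What remains is that the objectives name no comparator for either device and disagree with the comparator sentence.

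The second reply concerns size. Anxious has no stated cut-off. If selection rests on clinical judgement or on another measure, regression to the mean in VFAS could be smaller or absent. Scores around an injection, in children with no dental history, could rise. This also stands: a reader might take a fall as established, but the article fixes neither its size nor its direction. The confounding itself does not depend on either.

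Third, superiority over control may not be the aim, since the trial is labelled an equivalence trial and control is active. That is a reason to say which contrast the label covers. It does not rescue a device objective without a comparator.

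Finally, analysis detail may sit in a fuller document. The point here concerns what the stated objectives say, not detail left out of the article.

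**Conclusion.** The point holds in conditional form. As worded, no objective uses the randomised control arm, and objectives 1 and 2 evaluate each device before and after local anesthesia with no comparator. Answered that way, any change common to all arms is confounded with the device effect.

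The range of about 28-78% against 2.5% is an illustration. It rests on a paired test, 20 per arm, truncation on baseline VFAS at the top 30-50% and r of 0.5-0.7; allowing r up to 0.8 lowers the bottom of the range to about 20%. It should not be read as this trial's error rate. The structural conclusion needs none of these figures. It bears on the trial's main claim, that each device is effective, and the article reports the study as not yet started, so the objectives can still be corrected.

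**What to change.** Bring the objectives into line with the comparator sentence:

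- Objective 1: the difference in VFAS between kaleidoscope and control at a stated time after local anesthesia, adjusted for baseline VFAS.
- Objective 2: the same difference between VR goggles and control.
- Objective 3: keep as VR goggles versus kaleidoscope.
- Report within-arm changes descriptively, without efficacy claims.
- State to which contrast the equivalence label applies, since the device-versus-control questions concern a difference.

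The cost is rewording. The control children and the baseline VFAS are already planned, so no new participants or measurements are needed. The downside is that device-versus-control contrasts are less likely to reach significance with 60 children than within-arm tests. With an assumed 20 per arm, two-sided 0.05 and 80% power, the article's formula gives a detectable unadjusted difference of (1.960 + 0.842) × √(2/20) = 0.886 SD. That lower chance of significance is the price of a comparison that isolates the device effect.

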### Data analysis and statistical plan

Analytical tests like Chi square test and student’s t-test will be performed. All the statistical analysis will be performed using SPSS software, version 27.0 p<0.05 will be considered as the level of significance. This randomized clinical trial will be conducted at the Department of Pediatric and Preventive Dentistry, Sharad Pawar Dental College, Datta Meghe Institute of Higher Education and Research, Wardha. The allocation will be done using lottery method.

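### The trial is declared an equivalence trial but is sized and tested for a difference, with no margin and no named pair of arms, so its stated tests cannot establish equivalence

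*Protocol article*

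**What the plan says.** All of this is in the protocol article.

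- **Hypothesis type** (Protocol section, after the objectives): "It will be a trial for equivalence". No margin follows, and no pair of arms is named.
- **Objectives** (same section): the first two concern each technique before and after local anaesthesia. The third is the only between-group objective: "To compare effect of kaleidoscope and virtual reality goggles technique to reduce dental anxiety levels in young children before and after the administration of local" anaesthesia. None of the three mentions the control arm.
- **Arms**: kaleidoscope, virtual reality (VR) goggles and basic behaviour guidance as control. All three are put forward for comparison: "Comparators Kaleidoscope, Virtual reality goggles technique and conventional behaviour management method will be taken into consideration for comparing".
- **Sample size**: taken from an earlier study with a "similar study technique by using the sample size formula for difference between two means". The formula is shown in symbols only, with no values for the difference, the SDs, the power or the allocation ratio. The result is: "A total of 60 children will be included for the study".
- **Tests** (Data analysis and statistical plan): "Analytical tests like Chi square test and student’s t-test will be performed", with p<0.05 as the significance level.
- **Primary outcome**: the VFAS score.

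**The concern.** The declared hypothesis and the stated method point in opposite directions. The null hypothesis of a t-test is no difference, so p<0.05 is evidence against equality. An equivalence claim needs the reverse: differences as large as a pre-set margin must be rejected in both directions. Without a margin there is nothing to reject.

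At stake is what the trial may conclude on its primary outcome. If kaleidoscope and VR differ by a small or moderate amount, a trial of this size will more often than not return p≥0.05. In a trial labelled as equivalence, that result could be misread as showing that the two devices are interchangeable.

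**Working it through.** **1. The stated elements side by side**

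| Element | What is stated | Question it answers |
|---|---|---|
| Hypothesis | Equivalence | Is the difference smaller than a margin? |
| Sizing | Difference between two means | Can a difference Δ be detected? |
| Tests | Chi-square and t-test, p<0.05 | Is there a difference? |
| Objective 3 | Compare kaleidoscope and VR | Is there a difference, and how large? |

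The equivalence sentence is the only element that does not fit the others.

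**2. The plan's own figure**

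The total of 60 can be neither reproduced nor refuted, because no inputs are given. The formula can be solved backwards. Assume three equal arms (60/3 = 20), equal SDs, k = 1, two-sided 0.05 and 80% power:

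n = 2(z_α + z_β)² / d², so d = (1.960 + 0.842) × √(2/20) = 2.802 × 0.3162 ≈ 0.89.

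Twenty per arm therefore suits a standardised difference of about 0.89 to 0.91 (the range allows for rounding n up). At 90% power it is 1.03 to 1.05. This is a design for detecting a large difference.

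**3. How often the t-test is non-significant when a true difference exists**

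Assumptions: 20 per arm, common SD, two-sided 0.05, 38 degrees of freedom. The non-centrality parameter is d × √(20/2) and the critical t is 2.024.

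| True difference | Power | P(non-significant) |
|---|---|---|
| 0.3 SD | 15% | 85% |
| 0.5 SD | 34% | 66% |
| 0.8 SD | 69% | 31% |
| 1.0 SD | 87% | 13% |

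A non-significant result is the more likely outcome only when the true difference is below about 0.64 SD.

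**4. What an equivalence test could show with the same children**

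The half-width of the 90% confidence interval at the expected SD is t(0.95; 38) × √(2/20) = 1.686 × 0.3162 = 0.53 SD. The 95% half-width is 2.024 × 0.3162 = 0.64 SD.

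Power of two one-sided tests, each at 0.05, with zero true difference and 20 per arm:

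| Margin | Power |
|---|---|
| 0.3 SD | about 0% |
| 0.5 SD | 3% |
| 0.6 SD | 18% |
| 0.8 SD | 60% |
| 0.95 SD | 81% |
| 1.0 SD | 86% |

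The normal-approximation formula gives 80% power at (1.645 + 1.282) × 0.3162 ≈ 0.93 SD. With the t distribution the margin is slightly wider, about 0.95 SD.

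**5. Size needed for 80% power at a given margin**

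n per arm = 2(1.645 + 1.282)² / margin². For 0.5 SD this is 2 × 8.564 / 0.25 = 68.5, so 69 per arm, or 207 in three equal arms. For 0.8 SD it is 27 per arm (81), and for 0.3 SD it is 191 per arm (573).

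**The case against.** The strongest reply is that this is a condensed article and an analysis plan may exist unseen. The list of tests is open-ended (tests *like* these), so an equivalence test might be planned, and Δ in the formula might have been meant as a margin. The absence of a confidence-interval rule would not be a finding by itself. What does not fall to this reply is the conflict between things that *are* stated. The formula is labelled as one for a difference, no equivalence method is named, and an unseen plan cannot bring the label into line with the sizing and tests without changing one of them.

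Other parts of the objection stand and limit the point:

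- **A reader might infer that p≥0.05 will be reported as equivalence.** The article never says how equivalence will be concluded. This is a possible misuse, not a stated rule.
- **A reader might infer that any real difference would usually be missed.** That holds only below about 0.64 SD. At 0.8 SD the t-test misses the difference 31% of the time.
- **A reader might infer that no margin below 0.53 SD could ever be met.** A low sample SD occasionally narrows the interval enough, hence the 3% power at 0.5 SD.
- **A reader might take the aim to be superiority over control.** The aim and objectives name no comparison with control, and the control arm receives active behaviour guidance. It is sound to note that equivalence of the two devices would not by itself show that either works, but that is a point of interpretation, not the stated aim.
- **Twenty per arm is inferred.** Only the total is given, with simple random allocation and no ratio.

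**Conclusion.** The point holds as an inconsistency within the protocol: the declared equivalence hypothesis does not match the difference-based sizing and tests, no margin is set, and the arms to be equivalent are not named. As stated, the tests cannot establish what the trial is declared to test.

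The conflict itself follows from the text and needs no assumptions. The figures for its size rest on equal arms of 20, a common SD, and SD units in place of VFAS points, since the article gives no VFAS SD. They illustrate the problem and do not show that the design misses a stated target. On those assumptions, 60 children could support an equivalence claim with 80% power only if a difference of about 0.95 SD were accepted as negligible. That is slightly more than the 0.89 to 0.91 SD that the same numbers are suited to detect.

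This should be corrected before the trial starts, because it determines what may be concluded on the primary outcome. The article gives the study status as not yet started, so the correction can still be made without knowledge of any data.

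**What to change.** **Preferred.** Delete the equivalence sentence and state that the trial tests for differences, in line with the sizing, the tests and objective 3. Report kaleidoscope versus VR on VFAS as a difference with a 95% confidence interval, and report each device's difference from the control arm alongside it. State that p≥0.05 will not be called equivalence. This does not require new primary comparisons against control.

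**If the equivalence claim is kept.** Name the pair of arms (kaleidoscope versus VR). Fix and justify a VFAS margin before the start. Conclude equivalence only if the 90% confidence interval lies inside that margin. State the power that 60 children give for it, with the assumed SD.

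**Cost.** The first option gives up the equivalence claim; the second will probably show that it has low power unless the margin is wide. Either way this is more than an edit to the article: the trial is registered and has ethics approval, so any hypothesis wording held there must be amended to match before the trial starts. The first option needs no additional children.

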## Discussion

There is a limited literature available regarding the use kaleidoscope as a distraction method for children undergoing dental procedures. Aditya
*et al.* conducted a study to compare various methods of distraction to control anxiety in 60 children between the age group of six - nine years divided into four groups. Group 1 was fidget spinner (FS), Group 2 was kaleidoscope, Group 3 Virtual reality and Group 4 was control group with no distraction. The child’s self-reported anxiety levels using Venham’s picture test (VPT); the pulse oximeter was used to measure physiological signs of oxygen saturation and pulse rate at three intervals i.e. before, during, and after the IANB procedure. The VPT values were lower in the first three groups. Hence it was concluded that Fidget spinner, kaleidoscope, and virtual reality seem to be effective distraction methods and can be recommended as effective approaches to help reduce children’s dental anxiety during IANB procedures.
^
13
^ Tailor
*et al.* found out that when Virtual reality (VR) and on-screen audio-visual distraction techniques were used in the age group of 4-8 years the VPT scores were significantly reduced in VR group as compared to On-screen aid group in the first two visits that included procedures of screening, cavity preparation and L.A. administration.
^
14
^ The effect of cartoon display and kaleidoscope in children between the ages of 5-12years was assessed and the anxiety levels were scored using Children’s Fear Scale by Molu and Açıkgöz, during echocardiography procedure. A significant difference is evident in anxiety scores before and during between all the intervention groups and it was concluded that use of kaleidoscope is an effective measure in reducing anxiety.
^
15
^ Distraction by Kaleidoscope and VR is a promising area for future research in pediatric dentistry because of the rising interest in non-pharmacological methods for behaviour management.

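### Procedures and injection types are pooled under an unstratified lottery; drawing lots by planned injection type and modelling it would recover precision at almost no cost

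*Protocol article*

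**What the plan says.** The Protocol section of the article defines eligibility by need for local anaesthesia: children who "will undergo dental treatment requiring administration of local anesthesia for procedures like pulpectomy or extractions will be included in the study". The list of procedures is open-ended, and no injection technique is specified or excluded.

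Allocation is described without strata: "Sequence generation by lottery method will be generated", and "The participants in each group will be allocated by simple random sampling". The data analysis section repeats that a lottery is used. The total is fixed ("A total of 60 children will be included for the study") across three arms. The allocation ratio is not given, so 20 per arm is an inference.

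The primary outcome is the Visual Facial Anxiety Scale (VFAS) score. All outcomes are taken at three points around the injection, the last straight after it. The data analysis section gives chi-square and t-tests as examples of the tests, with no factor for procedure or injection.

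The sample size is said to rest on an earlier trial. According to the Discussion, that trial measured children around one injection type and presented its devices as "effective approaches to help reduce children’s dental anxiety during IANB procedures".

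**The concern.** The stimulus being measured is the injection. If injection types differ in how much anxiety they provoke, a mixed sample has more within-arm spread than a single-injection sample. Any variances taken from the earlier IANB study would not contain that extra spread. The Introduction also says that the "majority of significant triggers come from the sight, sound, and vibratory sensation of dental drills, and sensation of a local anaesthetic injection", so the protocol itself treats what is done to the child, and what the child expects, as drivers of anxiety.

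With about 20 children per arm, a simple lottery can also leave the arms with visibly different mixes. At stake are the sensitivity of the kaleidoscope versus virtual reality comparison and the ease of interpreting a trial whose arms turn out unbalanced. Precision matters all the more because the article declares an equivalence aim, and wider intervals make equivalence harder to show.

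**Working it through.** **Inputs from the article.** Total 60 children; three arms; significance level 0.05; unstratified lottery; t-test named.

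**Assumptions, not in the article.** Equal arms of 20; two-sided test; two strata (for example IANB and other) with a 50% or 30% share; a difference *g* between strata of 0, 0.5, 0.8 or 1.0 within-stratum SD in the anxiety score.

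**The plan's own figure.** The article shows a two-means formula but no difference, SD, power or ratio, so 60 can be neither reproduced nor refuted. Back-solving for 20 per arm at 80% power gives (1.960 + 0.842) × √(2/20) = 0.886 SD. That value serves below as the reference difference.

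**Step 1: chance of an uneven mix.** Let X₁ and X₂ be independent Binomial(20, p) counts of one stratum in two arms. A gap of 5 children is 5/20 = 25 percentage points.

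| Share p | Two given arms differ by ≥5 | Some pair of the three differs by ≥5 |
|---|---|---|
| 50% | 15.4% | 33% |
| 30% | 11.9% | 26% |

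**Step 2: what a 25-point gap does.** The mean difference shifts by 0.25 × *g*: 0.125, 0.20 or 0.25 SD for *g* = 0.5, 0.8 or 1.0. The standard error of the unadjusted difference at a 50% share is √[(1 + 0.25*g*²) × 2/20]: 0.326, 0.341 or 0.354 SD. Each shift is therefore less than one standard error.

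**Step 3: error rate.** In 40,000 simulated two-arm comparisons with no true device difference, the unadjusted t-test rejected in 5.0%, 5.0% and 4.9% for *g* = 0.5, 0.8 and 1.0. Among only those simulated trials with a gap of at least 5 children, it rejected in 6.2%, 8.7% and 10.6%.

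**Step 4: variance and power.** Pooling multiplies the within-arm variance by 1 + p(1 − p)*g*². At p = 50% that is 1.06, 1.16 or 1.25. At p = 30% (p(1 − p) = 0.21) it is 1.05, 1.13 or 1.21. Offsetting the 50% figures by enrolment would take about 60 × 0.0625 ≈ 4, 60 × 0.16 ≈ 10 or 60 × 0.25 = 15 more children.

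Simulated power for a true difference of 0.886 SD at a 50% share:

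| *g* (SD) | Simple lottery, unadjusted | Simple lottery, stratum in model | Stratified lots, unadjusted | Stratified lots, stratum in model |
|---|---|---|---|---|
| 0 | 78% | 77% | 78% | 78% |
| 0.5 | 76% | 77% | 76% | 78% |
| 0.8 | 72% | 77% | 73% | 78% |
| 1.0 | 69% | 77% | 70% | 78% |

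A normal approximation, Φ(0.886/SE − 1.96), gives 80%, 78%, 74% and 71% for the first column. The simulated values are about two points lower because the t-test is used.

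**Reading the table.** The model factor does most of the work and stratified lots add about one point. Stratified lots without the factor recover almost nothing: the ordinary t-test then becomes conservative, with type I error of 4.4%, 3.5% and 2.8% for the three non-zero values of *g*.

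**The case against.** The strongest case against the point has four parts.

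- **Chance imbalance is not bias.** A reader might infer that the procedure mix will pass for a device effect. The article does not support that. Under a randomised lottery the imbalance is already covered by the test's error rate, as Step 3 shows. The raised rates of 6.2% to 10.6% describe only trials that have already turned out unbalanced. This objection stands, and the point is not put as confounding. The article does have one person both generate and assign ("The co-investigator of the department will generate the allocation sequence and will assign participants to interventions"), but that is a separate matter of concealment.

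- **The drill comes after the measurement.** A reader might also infer that a child having a pulpectomy and one having an extraction meet different stimuli while being scored. The schedule ends straight after the injection, so the later treatment can act only through anticipation, and the children are dental-naive. This stands too, and it is why injection type is the better stratum.

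- **The effect size is assumed.** Nothing in the article gives a difference between procedures or injections. At zero there is no loss. This stands; the power figures are a range, not an estimate.

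- **An analysis plan could adjust.** The article's list of tests is only illustrative, an unseen plan might add a covariate, and analysing change from the pre-injection score could absorb some anticipatory difference. This stands in part: adjustment alone gives about 77%. But it needs the injection type to have been recorded, and no analysis plan can alter the unstratified allocation stated here.

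The earlier study is a precedent for one injection type only. The article does not say that it restricted the dental procedure.

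**Conclusion.** This is a cheap improvement, not a flaw that invalidates the comparison. The pooling and the unstratified lottery are stated, and the source study's single injection type makes the open mix a mismatch within the article itself. With 20 per arm and a 50:50 mix assumed, there is about a 15% chance that two given arms differ by 25 points or more, and about 33% that some pair of the three does. The overall cost is precision: roughly 2, 6 or 9 points of power for assumed stratum differences of 0.5, 0.8 or 1.0 SD, and none at zero. Overall type I error stays near 5% throughout. The article reports that the study has not started, so the allocation can still be changed.

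**What to change.** 1. Draw lots separately by planned injection type, IANB versus other. If only the procedure is known beforehand, use planned procedure with an 'other' category, because the eligible list is open. Put equal numbers of the three groups in each set of lots.
2. Record injection type and procedure for every child.
3. Include the stratum as a factor in the between-arm comparison of the VFAS score. Steps 1 and 3 belong together, since stratified lots without the factor gain almost nothing.

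**Cost.** One extra set of lots (two if an 'other' category is needed), one factor in the analysis and no added children. Power stays at about 78% even if the strata turn out not to differ. The downside is that the planned injection or procedure must be written down before the lot is drawn. The article does not say whether it is known by then.
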